## ***ABBREVIATION LIST***

|           |                                                                                                           |
|-----------|-----------------------------------------------------------------------------------------------------------|
| AHA       | American Heart Association                                                                                |
| CPP (IRB) | Comité de Protection des Personnes (Institutional Review Board)                                           |
| CNIL      | Commission Nationale de l'Informatique et des Libertés                                                    |
| CCTIRS    | Comité Consultatif sur le Traitement de l'Information en Matière de Recherche dans le Domaine de la Santé |
| CRF       | Case Report Form                                                                                          |
| EOOBM     | Early out of bed mobilization                                                                             |
| eCRF      | electronic case report form                                                                               |
| GCS       | Glasgow Coma Score                                                                                        |
| HAS       | Haute Autorité de Santé                                                                                   |
| ICH       | International Conference on Harmonization                                                                 |
| ID        | Identifier                                                                                                |
| INSERM    | Institut National de la Santé et de la Recherche Médicale                                                 |
| ITT       | Intent to treat                                                                                           |
| PP        | Per protocol                                                                                              |

## ***INTRODUCTION***

In common practice, stroke patients are usually kept in bed with the upper body inclined at 30° maximum during the acute stroke phase. Nevertheless, the duration of this positioning has never been clearly defined in clinical trials. As stroke mostly involves the elderly, immobilization can have adverse effects on the clinical outcome, on the rate of complications during hospitalization, and the return to a normal level of activity. On the other hand, clinicians may be fearful to trigger a potential neurological worsening while using early out of bed mobilization (EOOBM) procedures, particularly if the patient has been diagnosed with a common or internal carotid artery stenosis.

In this study, we hypothesize that early mobilization could improve the outcome of stroke patients, decrease the rate of immobilization related complications, and shorten the length of stay. Therefore we are testing here two out of bed mobilization procedures during the acute phase of stroke: « early » versus « progressive » upright positioning.

# **1. JUSTIFICATION OF THE STUDY**

## **1.1. BACKGROUND**

### **Recommendations from groups of experts regarding upright positioning procedure during the acute phase of stroke**

There is no national or international recommendation based on randomized control trials so far. Therefore, horizontal or 30 degrees positioning is admitted as the common practice. According to the « Haute autorité de santé » report (2009), « a lying down positioning with the head elevated at 30 degrees could contribute in the prevention of cerebral edema ».  In the same fashion, strict 0 degree lying down could improve cerebral perfusion initially.  Experts from the AHA relate that out of bed activity usually starts as soon as the patient is stable, but don't give any specific recommendation.  At the European level, no specific recommendation is proposed either.  This lack of guidelines leads to a heterogeneous practice. Another strategy to get the patient out of bed is to wait for the results of the ultrasounds before seating the patient. The drawback of this strategy is that it relies on the ultrasound exam availability, so the patient may stay in bed longer than required.

### **EOOBM may decrease the rate of complications linked to prolonged immobility**

Complications associated with immobility are: deep vein thrombosis, pneumopathy, urinary tract infections, constipation and pressure sores.  In the setting of stroke, a study led in Denmark showed that, over 11757 patients, 2969 (25.3%) presented at least one complication during hospitalization: Urinary tract infections (15.5%), pneumopathy (8%), and constipation (7%). 

In this study, early mobilization within the first 24 hours after stroke onset significantly decreased the complication rate. These results were confirmed by several pilot studies comparing the « usual » procedure to early out of bed activity. Indeed, mobilized patients showed less pneumopathy, urinary tract infection and fall. 

### **A particular situation: acute stroke associated with carotid artery stenosis**

In some patients, neurological deficit could be aggravated during early positioning, particularly in the presence of a significant carotid artery stenosis. Indeed, cerebral autoregulation is impaired at baseline in those patients.  In such cases, it is possible that the patient displays neurological deficit in situations that challenge cerebral hemodynamics, like standing from a chair, or a decreased sight under bright light.  This can be related to what we may call « hemodynamic » cerebral infarction, even if the pathophysiology of these ischemic cerebral injuries is still a matter of debate: hemodynamic and microembolic hypotheses are discussed.  The « post conditioning » concept, which consists of short additional moderate hypoperfusion applied to the ischemic area, could be related to patients with carotid stenosis. These transient periods of hypoperfusion have also been shown beneficial in some studies. 

### **EOOBM may be beneficial to patient outcome**

EOOBM (first days after stroke), in addition to decreasing the risk of complications related to immobility, doesn't seem deleterious to stroke patients.  The results of two phase 2 studies have recently been published in the journal Stroke.  This publication combines and

analyses the results of two pilot studies: AVERT (Australia) and VERITAS (UK). VERITAS was a prospective study to explore the feasibility of early out of bed activity after stroke (ischemic and hemorrhagic) and has included 32 patients. The study AVERT was a randomized controlled trial, that enrolled 71 patients (ischemic and hemorrhagic stroke), and focused on feasibility and immobility related complications. In AVERT, early out of bed activity (<24 hours) was compared to an « usual » protocol (not described in detail).

In those two publications, the protocol for the first upright positioning is not precise, and the status of the internal carotid artery (presence/absence of stenosis) is not reported. The meta analysis of the two studies combined showed an improvement of the prognosis at 3 months (Rankin score) in the group that was mobilized early.

## **Aim of the study**

In this study, we want to test whether early out of bed mobilization (sitting) after stroke improves patients' prognosis at 3 months, and limits complications related to immobility. Secondary parameters such as length of stay and autonomy levels will also be investigated.

## **Perspectives**

- **Improve stroke patients care during the acute phase**
- **Decrease complication rate in this population**
- **Socio economic impact (decrease of economic burden) through a decrease in hospital length of stay and a better recovery**

Bibliography is given at the end of the proposal.

## **1.2. RISKS AND BENEFITS FOR THE ENROLLED PATIENTS**

### **1.2.1. Benefits**

#### **1.2.1.1. At the individual level**

Specific follow up after stroke will be undertaken, especially through a mandatory follow up visit at 3 months post stroke.

#### **1.2.1.2. At the collective level**

This work will predominantly benefit stroke patient in general. Results of this study will have an impact on everyday clinical practice, which would also be more homogeneous. Stroke patient care will be optimized. The socio economic impact of this work could be important if the hypothesis tested is verified, through the diminution of the length of stay, and a better patient outcome. In France, cerebral ischemia involves about 150 000 persons a year.

## 1.2.2. Risks

### 1.2.2.1. Individual level

#### ➤ Risks and physical constraints

This study doesn't imply any physical constraint to the patient. Out of bed positioning is performed routinely in stroke units.

#### ➤ Risks associated with the disease studied

- Neurological worsening
- Seizure
- Sequellae with limitation of autonomy (sensorial-motor deficit, aphasia, loss of sight, gait disturbance, cognitive impairment)
- Decrease level of consciousness
- Coma
- Death

#### ➤ Risks associated with the procedure studied

Major side effects could be observed:

- Neurological worsening defined by aggravation of the existing deficits (motor, aphasia,..) or occurrence of new neurological deficits during or within the first 5 minutes after upright positioning.
- Fall that can be complicated by fracture

A complete list of the side effects can be found in the vigilance section (see infra).

#### ➤ Psychological risks and constraints

None identified

#### ➤ Socio-economic risks

Caused by the disease: incapacity to resume work, to get a loan, and possible increase in the insurance fees.

### 1.2.2.2. Collective risk

None identified

## 1.2.3. Risk-benefit ratio

The main risk of the study relies on the possibility of neurological worsening, a side effect that can spontaneously occur during the disease natural history, even without any mobilization of the patient. The physician may be fearful of this outcome, which usually leads to a more prolonged immobility for the patient. It increases the length of stay and the risk of complications (urinary

tract infection, constipation, deep vein thrombosis...), and also delays the ability to return to the former level of autonomy. Data from literature, even though incomplete, don't seem to show that EOBBM is associated with a poor outcome. Risks that are taken in this study regarding neurological worsening are therefore low, for a potential benefit at the population scale, improving patient outcome, but also alleviate the socio economic burden of stroke.

## **2. AIMS AND ENDPOINTS**

### **2.1. PRIMARY AIM AND EVALUATION CRITERIA**

#### **2.1.1. Primary aim**

To show that the functional prognosis of stroke patient at 3 months after stroke onset is better in the « early sitting » group compared to the « progressive sitting » group.

#### **2.1.2. Primary outcome**

Functional prognosis at 3 months evaluated using the modified Rankin score. Proportions of Rankin score [0-2], which correspond to an autonomous life, will be compared between the two groups.

### **2.2. SECONDARY AIMS AND EVALUATION CRITERIA**

#### **2.2.1. Secondary aims**

To show that neurological deficits observed at 7 days and 3 months after stroke onset are improved in the « early sitting » group.

To show that the functional prognosis at 7 days after stroke onset is improved in the « early sitting » group.

To show that autonomy is improved at 7 days and 3 months in the « early sitting » group

To show that early sitting facilitates the process of going back home

To show that the length of stay is shorter in the « early sitting » group

To show that early sitting decreases the rate of complications related to immobilization.

To explore the tolerance of upright positioning in the two groups

To explore the prevalence of fatigue at 3 months after stroke in both groups.

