| Objectives                | 
Principal aim:
To show that functional prognosis, at 3 months after ischemic stroke, is better for the patients mobilized out of bed early, compared to the ones progressively mobilized out of bed.
 
Secondary aims:
 
 
- To show that neurological deficits (NIHSS) observed at 7 days and 3 months after stroke are improved in the Early out of bed mobilization (EOOBM) arm.
 
- To show that the functional deficit at 7 days is better in the “early” mobilized group.
 
- To show that the level of autonomy is improved at 7 days and 3 months in the “early mobilization” group.
 
- To show that EOOBM increases the chance for the patient to be back home faster
 
- To show that the length of stay is shorter in the “early mobilized” group
 
- To assess the tolerance of the EOOBM in both groups
 
- To show that EOOBM decreases the rate of immobility related mobilization
 
- To assess the impact of the two upright positioning procedures on the post stroke fatigue at 3 months
 
 |
| # of patients required    | 400 patients                                                                                                                                                                                                                                                                                                                                                                                                                                                                                                                                                                                                                                                                                                                                                                                                                                                                                                                                                                                                                                                                                                                              |

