#### Secondary outcome

- Clinical score (neurological deficit) based on the NIHSS at 7 days and 3 months: comparison of the mean scores between the two groups using a Student's test.
- Functional scale (Rankin score) at 7 days: comparison of the proportions of patients with a score [0-2] by a Chi square test.
- Autonomy scale (Barthel index) at 7 days and 3 months: comparison of the proportions of patients with a score < 60 (dependent) between the 2 groups using a Chi square or a Fisher test
- Length of stay: comparison of the means between the two groups using a Student's test
- Percentage of patient back home before 7 days or 3 months: Chi square test or Fisher test.
- Side effects associated with sitting in the two groups (tolerance of upright positioning in the early versus progressive arms) : description of the side effect in the 2 groups and comparison of the most frequent (>5%) by a Chi square test or a Fisher test.

- Prevalence of swallowing disturbance, pneumopathy, acute urinary retention, bladder catheterization, deep vein thrombosis during hospitalization: comparison between the two groups using a Chi square test or a Fisher test.
- Prevalence of post stroke fatigue: comparison between the two groups using a Chi square test or a Fisher test.

A multivariate logistic regression model will be used in a second step to adjust on age and former (before the qualifying event) Rankin score.

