### **6.2.2. Statistical justification for the number of patients required**

In a meta-analysis of two pilot studies comparing an « early » to a « usual » mobilization procedure, Craig and coll. (9) showed that the percentage of patients with a Rankin score [0-2] was 34.7 % at 3 months in the « usual » group (n=49) versus 57.4 % in the « early » group (n=54).

In our study, we hypothesized that the functional outcome at 3 months assessed by the Rankin score will be better in the « early » group than in the « progressive » group, with a percentage of Rankin [0-2] of 35% in the « progressive » group and 50% in the « early » group. With an alpha risk of 5% and a power of 80% (bilateral), 183 patients per group are required to show a difference. Total number will then be 366 patients.

Percentage of poor tolerance during the first sitting is estimated between 5 and 10% in the 2 groups. As this may affect the Rankin score at 3 months, the number of patient to include has been increase to 400.

If the superiority of the « early » group is not statistically demonstrated, a switch to non inferiority could be undertaken. For this analysis, the non inferiority threshold is set at -5 % (maximum acceptable clinical difference). With 400 patients, non inferiority will be demonstrated if the real difference between the two groups is between 9 and 15%.

Reference: Committee for Proprietary Medical Products (CPMP). Points to consider on switching between superiority and non inferiority. 2000. European Medical Agencies (AMEA). CPMP/EWP/492/99.

The study will be undertaken in 11 centers. Each one, has the potential to recruit patients, with at least 300 cerebral infarction cases a year.

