### **6.2.3. Significance**

Significance is set at 5%. If a witch to non inferiority is done, bilateral confidence interval of 95% will be built and the inferior border will be compared to the non inferiority threshold set at -5%.

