#### **6.2.8. Randomization**

The randomization list will be created by a statistician from the clinical research department of Nantes university hospital. Randomization will be performed using blocks and a ratio of 1:1.

A sealed envelop that contains the randomization # and the group affiliation will be created for each patient. These envelops will be numbered and stored in each participating center. Each time a patient is included, the investigator will take the next envelop, following the numerical order.

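### Six secondary aims are worded as benefits to be shown and tested with about 13 comparisons under an unrestricted 5% level, so the chance of a false benefit is about 17% (10–28%), not 2.5%

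*Protocol*

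**What the plan says.** Section 2.1.1 of the protocol states the primary aim as something to be shown. Section 2.2.1 uses the same verb for six secondary aims: neurological deficit, function at day 7, autonomy, return home, length of stay and immobility complications. Two examples are "To show that autonomy is improved at 7 days and 3 months in the « early sitting » group" and "To show that early sitting decreases the rate of complications related to immobilization". The two remaining aims, tolerance and fatigue, are to be explored. The abstract uses the claim wording for the same six, for example "To show that the length of stay is shorter in the “early mobilized” group".

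Section 6.2.1, under the secondary outcome heading, gives each outcome and time point its own comparison. The immobility aim is handled as "Prevalence of swallowing disturbance, pneumopathy, acute urinary retention, bladder catheterization, deep vein thrombosis during hospitalization: comparison between the two groups using a Chi square test", with Fisher's test as the alternative; that is, five complications are compared one by one. An adjusted logistic model follows as a second step.

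Section 6.2.3 reads "Significance is set at 5" per cent and does not tie that level to the primary outcome. Section 6.2.6 announces an analysis plan before database freeze that will detail changes to the statistical section.

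**The concern.** The protocol draws its own line between claims and exploration and puts six secondary aims on the claim side. It then gives those aims many tests and one level for all. Four of the six aims have more than one comparison. The immobility aim speaks of one complication rate but is tested as five separate complications, and nothing says what pattern of results would count as having shown it.

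This matters most if the primary superiority test fails. Sections 6.2.1 and 6.2.2 foresee that case and switch to non-inferiority. The benefit message would then rest on secondary outcomes such as length of stay, which section 1.2.1.2 links to the trial's socio-economic impact. As written, a single nominal p<0.05 could be reported as a demonstrated benefit. The trial is also open-label, a further reason not to treat one such result as proof.

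**Working it through.** **The plan's own figure.** Section 6.2.2 assumes, for the primary outcome, "with a percentage of Rankin [0-2] of 35% in the « progressive » group and 50% in the « early » group", and concludes "With an alpha risk of 5% and a power of 80% (bilateral), 183 patients per group are required to show a difference". Section 6.2.8 gives the allocation: "Randomization will be performed using blocks and a ratio of 1:1". With mean proportion 0.425:

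n = [1.960·√(2·0.425·0.575) + 0.842·√(0.35·0.65 + 0.50·0.50)]² / 0.15² = 169.3, so 170 per group.

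With the continuity correction, n·[1 + √(1 + 4/(n·0.15))]²/4 = 182.4, so 183 per group and 366 in total. The stated figure is reproduced as a two-sided 5% calculation for the primary outcome alone. The protocol gives no error rate for the secondary tests.

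**Count of comparisons serving the six claim-worded aims (section 6.2.1).**

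| Aim | Comparisons |
|---|---|
| NIHSS, day 7 and month 3 | 2 |
| Rankin 0–2, day 7 | 1 |
| Barthel below 60, day 7 and month 3 | 2 |
| Back home, day 7 and month 3 | 2 |
| Length of stay | 1 |
| Complications | 5 |
| **Total** | **13** |

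The total is 12 if return home is meant as one test. Fatigue and side effects are left out because their aims are worded as exploration.

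**Chance of at least one false benefit.** Only results in favour of early sitting can be read as showing these aims, so each test contributes 2.5%. For k independent tests the chance is 1 − 0.975^k. For k = 13 this is 28.0%, and for k = 12 it is 26.2%.

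The outcomes are surely correlated, but the protocol gives no correlations, so they are assumed. For k normal statistics with common correlation ρ, the chance is 1 − ∫ φ(u)·Φ[(1.96 − √ρ·u)/√(1−ρ)]^k du:

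| Assumed ρ | 13 tests | NIHSS and Barthel each needed at both times | Immobility aim, 5 tests |
|---|---|---|---|
| 0 | 28% | 20% | 12% |
| 0.3 | 21% | 17% | 11% |
| 0.5 | 17% | 14% | 9% |
| 0.8 | 10% | 8% | 6% |

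The third column treats NIHSS and Barthel as two pairs that must each succeed twice and leaves the other nine tests single. At ρ = 0 it is 1 − (1 − 0.025²)²·0.975⁹ = 20.5%. At ρ = 0.5 one such pair alone has a false-benefit rate of about 0.5%, so that reading is not inflated for those two aims. The rest of the family still is.

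The last column is an upper figure, because Fisher's test is conservative for rare events. With 200 per group its true two-sided size is about 1.7% at an assumed 2% event rate and 2.9% at an assumed 5%.

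**The case against.** The strongest objection is that multiplicity among secondary outcomes is commonly settled in the analysis plan, which is not at hand; that these outcomes are already labelled secondary; and that only the primary is powered. This stands as far as it goes: the absence of a hierarchy or a gate is not, alone, a fault of the protocol. What remains is what the protocol itself fixes, namely claim wording shared with the primary aim and a 5% level with no stated limit. Section 6.2.6 promises to detail modifications. It does not promise a multiplicity rule, and the aims sit in section 2.

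A second objection is that section 2.2.1 names both time points for neurological deficit and autonomy, which reads naturally as requiring both. That is fair, and it lowers the figure from 17% to 14%. It does not settle return home or the five complications.

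A reader might also infer more than the documents support:

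- *That a chance benefit is likely.* It is not: 17%, and 28% at most under the 13-test count.
- *That the relevant rate is 33% (19–49%) for the family, or 18% (13–23%) for the immobility aim.* Those figures count results against early sitting, which cannot be read as showing its benefit.
- *That letting the crude or the adjusted analysis count raises the either-direction rate from 33% to about 42%.* That figure gives every one of the 13 tests an adjusted version. The planned model is logistic, while NIHSS (two tests) and length of stay are compared as means, so at most 10 have one. It also rests on an assumed correlation of 0.92 between versions.
- *That the plan says any one significant complication proves the immobility aim.* No section says so; the protocol leaves the rule open.

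**Conclusion.** The point holds in a limited form. The protocol words six secondary aims as claims and tests them with about 13 comparisons (12 if return home is one) under a 5% level not confined to the primary outcome. With no true effect, the chance of at least one nominal result in favour of early sitting is about 17%, or about 14% if NIHSS and Barthel need both time points. That is roughly six to seven times the 2.5% of a single test (14/2.5 = 5.6; 17/2.5 = 6.8). Across assumed correlations of 0.8 to 0 the ranges are 10–28% and 8–20%. For the immobility aim alone it is at most about 9% (6–12%).

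These sizes rest on an assumed common correlation, on no effect on any secondary outcome, and on the general 5% sentence applying to each test, which no section repeats test by test. The primary comparison is not touched. The change is worth making because it is cheap, but it does not threaten the trial's main conclusion.

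**What to change.** In section 2.2.1 and the abstract, reword the six secondary aims as exploratory or supportive. Add to section 6.2.3: *The 5% level applies to the primary outcome only. Secondary outcomes are supportive; they are reported as estimates with 95% confidence intervals and nominal p-values, and none will be presented as demonstrated.*

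If the sponsor wants to keep a secondary claim, test it only after primary superiority is shown, with one stated deciding rule per aim and a multiplicity procedure such as Holm's across the aims. With no effect anywhere, that gate alone caps the chance of a false secondary benefit at 2.5%. This route is a matter of choice; the relabelling is enough.

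Before any composite complication outcome is defined, reconcile the two lists. Section 2.2.2 names urinary tract infection where section 6.2.1 names acute urinary retention, and the abstract carries the same mismatch.

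The cost is wording only, with no extra patients, visits or data. The downside is that a nominal p<0.05 on a secondary outcome can no longer be called shown.
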